### Data quality

#### Data completion and homogeneity

To ensure the best level of data completion and homogeneity, a number of tools have been developed by the study team and shared with the centers:
detailed completion guidelines for clinical eCRF and epidemiological questionnaires;Standard Operating Procedures for patient inclusion, template of excel sheets to plan follow-up timepoints, visuals for face-to-face interviews (e.g. contraceptive packaging);regular contacts between the project managers and the CRA: in-person initiation visit (4 h), check-up calls after the first interviews, CRA meetings (on the sidelines of the LYSA congress);regularly updated Frequently Asked Questions (FAQ);listings of missing data or missing documents and upcoming follow-up timepoints.

Moreover, a center specific report summarizing the data of the centers and comparing their data to the whole cohort population is produced and sent to each center twice a year. Finally, local investigators are all part of the Scientific Committee and receive the minutes.

#### Data validation

A strong data validation system inspired from clinical research standards has been implemented and is regularly running, with different levels of data checking. First, the electronic data entry system contains automatic checks performed at regular intervals for data completeness and consistency. Second, a scientific review is conducted by the study team to guarantee scientific coherence of data. Last, a medical review is performed by center investigators to ensure overall clinical data coherence of major endpoints (e.g. treatment plan, staging, response to treatment, events during the follow-up like progression, relapse or death). In case of incoherence and when deemed necessary, queries are generated and sent to the centers. Corrections are edited in the eCRF and tracked in the audit trail. At regular intervals, the overall completeness and quality of the data is assessed.

Epidemiological data are systematically checked for aberrant or missing data. If there is extensive missing data or if clarification is needed, the CRA in charge of the interview is contacted.

### Biological samples

For the first 2500 patients included in REALYSA, blood samples will be collected at baseline (before any treatment), during first-line treatment, at end of first-line treatment and at relapse. Additional blood samples are also collected for patients with anaplastic lymphoma kinase positive (ALK+) anaplastic large cell lymphoma (ALCL), for specific analyses on antibodies and nucleophosmin (NPM) transcript. Details are presented in Table 3. In case of premature first line treatment discontinuation (before cycle 3), the samples will be drawn at the time of treatment discontinuation.

**Table 3 Tab3:** Biological sampling plan

Sampling	Banking constitutional DNA	Banking plasma	Banking serum	NPM-ALK^b^ (ALK+ ALCL)^c^	Anti-ALK Ab^d^ (ALK+ ALCL)
Baseline^a^	x	x	x	x	x
Day 1 Cycle 3		x		x	
End of first-line treatment		x		x	x
First relapse		x		x	

^a^before any treatment

^b^*NPM* Nucleophosmine

^c^*ALK+ ALCL* anaplastic lymphoma kinase positive anaplastic large cell lymphoma

^d^*Ab* Antibodies

### Virtual tumor biobank

The standard management of patients for their pathology includes taking tumor biopsies to establish the diagnosis. The remaining tumoral material (biopsy included in paraffin or frozen) will be requalified for research and stored by the centers. This material could be requested for specific projects in the future.

### Statistical analysis

#### Sample size calculation

No sample size calculation is strictly required for cohort studies but was needed for planning and funding perspectives. We have therefore used a pragmatic approach, based on one of the objectives of the study, which is to be able to detect an association between the exposure of interest and the clinical outcome of interest (e.g. response to treatment, progression-free survival, overall survival – see section on clinical outcomes) for a given lymphoma subtype. First, using lymphoma incidence rates [3, 39] in the geographical study zone, we estimated the number of new lymphoma cases that could be recruited in REALYSA over a 4-year recruitment period. Second, we calculated the hazards ratio (HR) that this study would be able to detect as a function of the number of events, which can be then back transformed to a number of patients of a given lymphoma subtype.

Firstly, based on the initially planned recruiting centers, we would expect 2796 new lymphoma cases yearly, so a total of 11,183 new cases during the 4 years of inclusion (unpublished data coming from an extraction of registry data). Considering a participation rate of 70% and an improving dynamic recruitment rate (40% during the 1st year, 75% the 2nd year, and 100% on the last 2 years), the number of cases that could be recruited in REALYSA is around 6000 patients (exactly 6165 patients, distributed as follows: 911 patients with HL, 2123 patients with DLBCL, 1294 patients with follicular lymphoma (FL), 344 patients with mantle cell lymphoma (MCL), 88 patients with Burkitt lymphoma, 958 patients with MZL and 447 patients with NHL-T).

Secondly, we calculated the detectable HR assuming a binary exposure of interest (say “present” vs “absent”). We relied on the proportional hazard model to describe the association between the exposure and the mortality hazard, with a 2-sided test at α = 0.05 (type 1 error rate) and a desired 80% power (i.e. 1 minus the type 2 error rate). With a pre-specified value for the prevalence of the exposure in our sample, we can obtain the detectable HR as a function of the number of events [40]. In order to get an absolute measure of the difference between groups (as opposed to the HR, which is a relative measure), one could use the link between HR and survival. This would allow to express the difference between the survival of the exposed, *S*_1_(*t*), and the unexposed *S*_0_(*t*) as: *S*_1_(*t*) = *S*_0_(*t*)^*HR*^.

We investigated scenarii with 3 levels of prevalence for the exposure: 10, 20 and 30%. The results are shown in Fig. 3 with the detectable HR according to the number of events. We would need to observe 530 events to be able to detect a HR of 1.5 with a type I error rate of 0.05, a power of 0.8 and an exposure prevalence of 10%. Therefore, if we assume that the proportion of events among the cases is approximately 30% (as observed for example for DLBCL for 1-year survival in France [7], and assuming no lost-to-follow up), then we need to observe 1767 patients with DLBCL (530/0.3). This HR of 1.5 in the context of DLBCL would then correspond to a 1-year survival of 70% in the unexposed group vs 59% in the exposed group. Despite the fact that this approach for sample size calculation relies on many assumptions, it has the advantage of being general and versatile to our different settings (i.e. according to lymphoma subtype and clinical outome of interest).

**Fig. 3 Fig3:**
[figure not shown]
Detectable hazard ratio according to the number of events for different levels of exposure prevalence

Consequently, the sample size was set at 6000 patients, as a good balance between feasibility and statistical power, at least for most common subtypes (i.e. DLBCL, FL and HL).

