## Background

Lymphomas comprise a heterogeneous group of more than 80 distinct entities classified on the basis of morphological, phenotypic, genotypic, and clinical characteristics [1]. Their age-adjusted incidence rates worldwide are more elevated in the most developed countries [2]. In France, they represent two thirds of hematopoietic cancers with an estimated 28,000 incident cases in 2018 (2000 Hodgkin lymphoma (HL) and 26,000 Non-hodgkin lymphoma (NHL)) [3]. The time trends in incidence over the last 30 years show an increase for most of the lymphoma subtypes (e.g. HL, follicular lymphoma (FL), diffuse large B-cell lymphoma (DLBCL), Marginal Zone Lymphoma (MZL) or Non-cutaneous mature T-cell lymphoma) [3]. This increase may be partly explained by the growing and ageing general population, as well as a better access to diagnosis and treatment. But other risk factors are suspected to be involved in the rising incidence [3]. Epidemiological studies have identified various factors associated with lymphoma onset, including socio-demographic factors, infectious disease status, family and medical history, lifestyle as well as occupational exposures (reviewed in Morton et al. [4]). There is a large etiologic heterogeneity among subtypes, with shared and distinct factors depending on subtypes, suggesting both subtype-specific and shared underlying mechanisms.

As for patient care, treatment efficacy greatly varies depending on histological lymphoma subtypes. Over the past 15 years, numerous therapeutic innovations have marked the treatment of lymphomas. For example, overall survival of patients with some main subtypes, including DLBCL, improved substantially in the last two decades with the introduction in 2003–2006 of anti-CD20 monoclonal antibodies in combination with chemotherapy as a first-line treatment [5, 6]. These innovations impacted the survival of patients with lymphoma, estimated in the general population. In France, data from population-based cancer registries (PBCR; FRANCIM network) showed an improvement in net survival over time clearly observed for DLBCL and FL (+18% between 1995 and 2010) whereas Hodgkin lymphoma survival remained stable (although very favorable) [7]. These encouraging results concerning the survival of lymphoma were also observed at European level [8].

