Several weaknesses may be identified in this study. First, unlike other cohorts (e.g. HMRN), not all lymphoid malignancies are included in REALYSA. We elect not to include patients with chronic lymphocytic leukemia (CLL)/lymphocytic lymphoma, primary central nervous system (CNS) lymphoma and post-transplanted lymphoma as there are other national networks for these lymphoid malignancies and their managements are very distinct from other NHL subtypes. Similarly, primary cutaneous T-cell lymphoma that are mainly diagnosed, treated and followed by dermatologists specialized in this disease are not included. Second, depending on the subtypes, the statistical power may be limited in some cases. Indeed, the comprehensive occupational and domestic exposure questionnaire, associated with clinical data, will help in understanding the role of environmental conditions (including socio-economic status, social institutional context, social relationships, environmental exposures, individual behaviors, lifestyle) on lymphoma prognosis. Previous studies suggested the potential prognostic impacts of some environmental exposures on lymphoma patient outcome [25, 62]. The major issue of these studies is to have sufficient statistical power to prove an association depending on exposure prevalence, the sample size of the lymphoma subtype and the number of events. We think that for the most frequent lymphoma subtypes, such as DLBCL, FL and HL, the power would be satisfactory to detect some environmental conditions as prognostic factors. We recognize that infrequent lymphoma subtypes or for low prevalence exposures, results will be considered as exploratory and will need further replications for instance through international collaborations.

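### The sample size calculation shows adequate power for DLBCL only; the extension to FL and HL rests on no event proportion, is doubtful for HL mortality, and the list of most common subtypes skips MZL

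*Protocol article*

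**What the plan says.** Under Sample size calculation, the protocol article sets out a general method and one worked case. The method: "We relied on the proportional hazard model to describe the association between the exposure and the mortality hazard". Testing is two-sided at the 5% level and the target power is 80%. Exposure prevalences of 10%, 20% and 30% are considered. The worked case is at 10%: "We would need to observe 530 events to be able to detect a HR of 1.5". An event proportion of about 30%, taken from one-year DLBCL survival and with no loss to follow-up, turns 530 events into 1767 DLBCL patients.

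The same section projects recruitment by subtype: "911 patients with HL, 2123 patients with DLBCL, 1294 patients with follicular lymphoma (FL"), then MZL 958, T-cell 447, mantle cell 344 and Burkitt 88, in total 6165.

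The section closes by presenting 6000 as a consequence of this calculation, a compromise between feasibility and "statistical power, at least for most common subtypes (i.e. DLBCL, FL and HL"). The Discussion repeats the list for the most frequent subtypes: "such as DLBCL, FL and HL, the power would be satisfactory" for detecting certain environmental factors. On HL prognosis the Background says: "Hodgkin lymphoma survival remained stable (although very favorable").

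**The concern.** The closing statement covers three subtypes, but the arithmetic covers one. The text gives no event proportion, event count or required patient number for FL or HL. Fig. 3 is not shown, but by its caption it relates the detectable HR to the number of events for each prevalence, so it does not tell the reader how many events a subtype will have.

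FL and HL have fewer patients than DLBCL, and HL is described as having good survival, so its death count may be low. If the power statement does not hold there, the rationale for 6000 is weaker than stated for those subtypes, and a reader of an HL survival analysis could credit it with more power than it has. In addition, HL is named among the most common subtypes while MZL, which is larger in the plan's own projection, is not.

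**Working it through.** **Inputs from the protocol article.** Two-sided α = 0.05, power 80%, HR 1.5, prevalence p = 10%, 20% or 30%, event proportion 30% (DLBCL, one year), expected patients 2123 (DLBCL), 1294 (FL), 958 (MZL) and 911 (HL).

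**1. Reproduce the plan's figures.** Schoenfeld: D = (1.960 + 0.842)² / [p(1−p)(ln 1.5)²].
- p = 10%: 7.849 / (0.09 × 0.1644) = 530.5, matching the stated 530.
- Patients: 530 / 0.3 = 1767, as stated.
- Survival in the exposed: 0.70^1.5 = 0.586, the stated 59%.
- Recruitment: 11,183 × 0.70 × (0.40 + 0.75 + 1 + 1)/4 = 6165, as stated, and the seven subtypes sum to 6165.

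The calculation itself is correct.

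**2. Events needed for HR 1.5 at the other prevalences.** 299 at 20% and 228 at 30%.

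**3. Apply the only event proportion given (30%) to each subtype.** Power = Φ(√(D·p(1−p)) × ln 1.5 − 1.96).

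| Subtype | Patients | Events at 30% | Power, p = 10% | p = 20% | p = 30% | Detectable HR, p = 10% |
|---|---|---|---|---|---|---|
| DLBCL | 2123 | 637 | 87% | 98% | >99% | 1.45 |
| FL | 1294 | 388 | 67% | 89% | 96% | 1.61 |
| MZL | 958 | 287 | 54% | 79% | 88% | 1.73 |
| HL | 911 | 273 | 52% | 76% | 87% | 1.76 |

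Detectable HR (80% power) = exp(√(7.849 / [p(1−p)D])). Scaling from 6165 to 6000 patients changes little: 620, 378 and 266 events for DLBCL, FL and HL.

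**4. Event proportion needed for 80% power at HR 1.5.** Required events divided by patients:
- DLBCL: 25% at 10% prevalence (530/2123).
- FL: 41%, 23% and 18% at 10%, 20% and 30% prevalence (530, 299 and 228 over 1294).
- HL: 58%, 33% and 25% (530, 299 and 228 over 911).

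**5. Range for FL and HL.** The document gives no event proportion for either, so the first column below is an assumption. Cells give power at 10% / 20% / 30% prevalence, HR 1.5.

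| Assumed events | FL | HL |
|---|---|---|
| 10% | 28 / 45 / 56% | 21 / 34 / 43% |
| 20% | 50 / 74 / 85% | 38 / 59 / 71% |
| 30% | 67 / 89 / 96% | 52 / 76 / 87% |
| 40% | 79 / 96 / 99% | 64 / 87 / 94% |

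With 10% events in HL (91 events), the detectable HR is 2.66 at 10% prevalence and 1.90 at 30%.

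**6. Ranking.** By expected number: DLBCL 2123, FL 1294, MZL 958, HL 911. HL is fourth, 47 patients behind MZL.

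**The case against.** The 530-event figure belongs to the hardest of the three prevalence scenarios and is worked for DLBCL alone. Neither closing statement gives an HR, a prevalence or a power level for FL or HL. The Discussion offers a judgement limited to certain exposures. It also labels results exploratory for low-prevalence exposures as well as for infrequent subtypes, and 10% may be meant as low, although no threshold is given. The 30% is a one-year death proportion, whereas follow-up runs 4 to 9 years (Study design). The method is offered for response and progression-free survival as well as overall survival, so event counts may be higher. The article also says that a cohort needs no formal sample size calculation.

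Most of this stands, and it rules out some stronger readings that a reader might infer:
- That only DLBCL can reach adequate power. This holds only at 10% prevalence with the borrowed 30%. At that event proportion FL passes at 20% and 30% prevalence and HL passes at 30%.
- That FL is underpowered. At 10% prevalence it needs 41% events, which the documents neither support nor exclude.
- That the plan keeps the exploratory label for infrequent subtypes alone. It does not.
- That null FL or HL results would be taken as evidence of no association. The plan reports HRs with 95% confidence intervals, which would show the imprecision.

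None of this supplies the missing event proportion for FL or HL, and for HL mortality the difficulty extends to the easier prevalence scenarios. The subtype list remains inconsistent whatever the event rates. A full table by subtype and outcome might fairly be left to the full protocol; a power conclusion drawn in the article without its basis is another matter.

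**Conclusion.** The concern holds in a limited form. Adequate power is demonstrated for DLBCL and is not shown for FL. It is doubtful for HL mortality: even at 30% prevalence a quarter of HL patients would have to die, with no loss to follow-up, and at 10% prevalence 58% would, against survival that the article itself calls very favourable. How far HL falls short depends on a death proportion that the document does not give; 10% is used above only to illustrate. For HL outcomes with more events, such as progression-free survival, the document does not settle the question either way.

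Separately, naming HL but not MZL among the most common subtypes contradicts the recruitment projection. The gap is small and no calculation depends on it.

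This is worth correcting, but below must-fix. The design figures reproduce, no analysis changes, and the 6000 target also tracks the recruitment forecast of 6165.

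**What to change.** In the closing sentence of Sample size calculation and in the matching sentence of the Discussion:
- Limit the demonstrated power statement to DLBCL.
- For FL and HL, state the outcome, assumed event proportion and exposure prevalence under which 80% power at HR 1.5 holds, or else give the larger detectable HR. A short table of expected patients, expected events by outcome and detectable HR at 10%, 20% and 30% prevalence would do this.
- Treat HL overall-survival analyses, and any FL analysis that falls short, as exploratory, alongside the infrequent subtypes and low-prevalence exposures already so labelled.
- Correct the subtype list so that it agrees with the projection (MZL ahead of HL), or say on what other ground HL is named.

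The cost is text and at most one small table. No extra patients are needed; the stated power becomes less favourable.

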#### Representativeness analysis

One of the objectives of this program is to have a satisfactory representativeness of the included population as compared to patients diagnosed with lymphoma in the general population, thus allowing generalization of the results. Twice a year and for each sex-lymphoma subtype combination, we compare age distribution of incident cases between the national incidence estimates based on FRANCIM data [3] and the REALYSA cohort to monitor the evolution of representativeness. We also compare the distribution of the lymphoma subtypes between the national estimates and REALYSA. Comparison of the main confounders’ distributions (i.e. sex, age, lymphoma subtype, stage, performance status) is also done bi-annually between REALYSA centers, in order to identify potential bias in patients’ recruitment in specific centers. Moreover, two pilot *départements* (Gironde and Isère) covered by cancer registries have been chosen to cover an increased proportion of the population by opening 3 to 4 centers in the *département*. Specific analyses will be performed in these *départements* to conduct a fine-tuned analysis of the representativeness, which will be very helpful to adjust for the global cohort if necessary, using particular statistical techniques [41].

#### Clinical outcomes

The following clinical measures will be recorded at different timepoints: response to treatment, progression-free survival (PFS), event-free survival (EFS), time to next anti-lymphoma treatment (TTNLT), overall survival (OS). Other quantities of interest, such as the net survival, survival after progression, transformations, onset of second cancers will also be studied.

#### Generalities on the statistical methods for basic description of the association between the variables and time-to-event outcomes

Continuous variables will be summarized in tables displaying sample size, mean, standard deviation, median, and range; quartiles will also be presented when considered relevant. Categorical variables will be described in counts and percentages, including a specific category for missing data. Time to events will be described using Kaplan-Meier method, and survival probabilities (with the corresponding curves) will be provided with their 95% Confidence Interval (CI). For (semi-) competing risks setting (i.e. dealing with multiple event types), cumulative incidence functions will be our measure of interest.

Association between a categorical baseline prognostic factor and the time to event will be assessed by a two-sided log-rank test and quantified with a hazard ratio (HR) with 95% CI as estimated from a Cox model including only this variable as predictor. The continuous baseline prognostic factors will be categorized using the quantiles of their observed distribution and we will apply the same strategy as the categorical prognostic factors. Additionally, for the continuous factors, we will use their original version in a survival model (e.g. Cox or flexible parametric model) to estimate the (eventually time-dependent) HR associated with a 1-unit increase of the factor. Multivariable survival models will also be used for estimating conditional HRs for the main clinical and epidemiological factors. Time-updated prognostic factors will be analyzed using extensions of the survival models aforementioned.

Despite all the efforts made for representativeness, the cohort might end up not being representative of the French general population of lymphoma patients. In that case, statistical techniques such as covariate adjustment methods [42] or methods based on the Inverse probability weighting (IPW) technique [43] could be implemented to correct for this bias [41, 44]. In that regard, the REALYSA setting in which the recruiting centers are located in *départements* also covered by PBCR will be very useful.

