### Study population

#### Inclusion criteria

Patients meeting all the following criteria are considered for enrollment in the study:
Signature of the REALYSA consent form;Aged over 18 at the time of inclusion;Newly diagnosed with lymphoma in the last 6 months (180 days);Lymphoma subtype belonging to at least one of the 7 histological subtypes: Diffuse large B-cell lymphoma, Follicular lymphoma, Mantle cell lymphoma, Marginal zone lymphoma, T-cell lymphoma, Hodgkin’s lymphoma, Burkitt lymphoma.

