#### Exclusion criteria

Patients meeting any of the following criteria are excluded from enrollment:
Anti-lymphoma treatment already received (except pre-phase therapy: typically, corticosteroids, vincristine, cyclophosphamide and rituximab, alone or in combination);Documented HIV infection.

Details regarding included and excluded lymphoma subtypes can be found in Additional file 1.

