#### Follow-up

Timepoints for data collection during follow-up are described in Table 2. Clinical data, as well as lifestyle changes, new morbidities, professional situation and work stress, infertility issues, use of alternative medicine are collected using data from medical record or via self-administered questionnaires filled in by the patients. Follow-up of patients is performed every 6 months during the first 3 years and annually thereafter until year 9. Due dates for completing the follow-up are generated from the diagnosis date (i.e. date of biopsy).

**Table 2 Tab2:** Overview of data collection timepoints during follow-up

Collected data	Data source	M6	M12	M18	M24	M30	M36	Y4	Y5	Y6	Y7	Y8	Y9
Disease status at last hematology consultation	Patient medical record	x	x	x	x	x	x	x	x	x	x	x	x
Number of consultations and imaging exams	Patient medical record	x	x	x	x	x	x	x	x	x	x	x	x
Treatment lines^a^	Patient medical record	x	x	x	x	x	x	x	x	x	x	x	x
Response to treatment	Patient medical record	x	x	x	x	x	x	x	x	x	x	x	x
Adverse events	Patient medical record	x	x	x	x	x	x	x	x	x	x	x	x
Relapses/progressions/transformations^b^	Patient medical record	x	x	x	x	x	x	x	x	x	x	x	x
New malignancy	Patient medical record	x	x	x	x	x	x	x	x	x	x	x	x
New morbidities	Auto-questionnaire	x		x		x		x	x	x	x	x	x
Lifestyle	Auto-questionnaire	x		x				x		x		x	
Professional situation	Auto-questionnaire		x		x				x		x		x
Work stress	Auto-questionnaire (Siegrist questionnaire)		x		x				x		x		x
Quality of life	Auto-questionnaire (QLQ-C30 + lymphoma specific modules)		x		x		x			x			x
Social support	Auto-questionnaire (SSQ6)	x	x		x		x	x	x	x	x	x	x
Women sexual and reproductive health	Auto-questionnaire					x							
Health behaviors^c^	Auto-questionnaire						x			x			x
Date and cause of death	Patient medical record												
End of study: reasons for early termination	Patient medical record												

^a^detailed therapies, start/end dates, dose modality (full/reduced in chemotherapy), amount of Gray if radiotherapy, transplant and other surgeries

^b^dates, involvement, available documentation, method of evaluation used, staging

^c^including use of alternative medicine, screening behaviors

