### Ethics

The study is performed according to the declaration of Helsinki, and national laws and regulations for RIPH2 studies. The REALYSA study was approved by a French ethics committee (Comité de Protection des Personnes Ouest II - file number: 2018/46) and by the National Commission for data protection and freedom of information (CNIL - decision number: DR-2018-238). Written informed consent is obtained from patients before any data collection. A specific signed consent form is also obtained from each patient willing to participate in genetic studies that may be conducted on blood samples. Patients are free to refuse to participate or to withdraw from the study at any time. Collected data are anonymous and secure data management systems are used. Any substantial change of the protocol (e.g. number of centers, number of collected blood samples) will be validated by the ethics committee before implementation.

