Finally, there are three major challenges in this study. First, we will have to pay strong attention to recruitment dynamics and patient characteristics to avoid recruitment biases and to have a population as representative of the general population of lymphoma patients as possible. Strong guidelines are given to centers in order to recruit all patients meeting the inclusion criteria, without any distinction on age, general condition or clinical prognosis. Moreover, smaller and non-University centers were opened during the extension phase in order to capture a larger population of patients, including those treated outside University Hospitals. Interim analyses will be conducted in order to compare participants’ characteristics with registries data. Nevertheless, even if the cohort is not representative of the whole French population of lymphoma patients, we strongly believe that building such cohort will be of use for many research works despite the lack of representativeness, as long as the “scientific inference is still valid” [64, 65]. The second challenge is the retention of patients in the cohort. Prospective follow-up is tied to the diagnosis date, in order to follow clinical management (e.g. annual follow-up from diagnosis), thus facilitating patient engagement. Newsletters with information on the study and projects will be sent to patients, in order to create a sense of belonging to the study. A dedicated webpage has also been created and updated with information on study and projects. Lastly, we aim to involve patients as partners of this research in order to facilitate communication and feedbacks between the research team and the patients included in the cohort and eventually minimize the attrition rate. Finally, as for all real-world studies, data completeness remains a major challenge. However, this study being conducted by investigators and CRA belonging to the hematological departments, we trust that this will maximize our capacity to recover satisfactory data.

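### Entry is open until 180 days after diagnosis but no delayed entry or endpoint time origin is stated, so survival counted from diagnosis would be overstated

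*Protocol article*

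**What the plan says.** **Entry.** Under Inclusion criteria a patient qualifies if "Newly diagnosed with lymphoma in the last 6 months (180 days" and on "Signature of the REALYSA consent form". The Ethics section adds: "Written informed consent is obtained from patients before any data collection". Under Exclusion criteria, "Anti-lymphoma treatment already received (except pre-phase therapy" rules a patient out, so pre-phase is tolerated and any other treatment before inclusion is not.

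**Clock.** The Follow-up section states: "Due dates for completing the follow-up are generated from the diagnosis date (i.e. date of biopsy". The Discussion repeats the anchor: "Prospective follow-up is tied to the diagnosis date, in order to follow clinical management".

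**Analysis.** The section on general statistical methods states: "Time to events will be described using Kaplan-Meier method, and survival probabilities (with the corresponding curves) will be provided". A categorical baseline factor "will be assessed by a two-sided log-rank test and quantified with a hazard ratio (HR" from a Cox model. Continuous factors go into Cox or flexible parametric models, and competing risks are handled by cumulative incidence functions. The Clinical outcomes section lists response, PFS, EFS, time to next anti-lymphoma treatment and OS, with net survival among further quantities. No start point is given for any of them. Delayed entry, left truncation and landmarking are not mentioned.

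**Correction foreseen.** If the cohort proves unrepresentative, covariate adjustment or inverse probability weighting may be used.

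**The concern.** A patient who dies between biopsy and consent can never be in the cohort. Every included patient has therefore survived from biopsy to consent by design. If the survival clock starts at biopsy and the risk set contains all included patients from day 0, that interval adds person-time in which no death can be recorded. Kaplan-Meier survival is then too high, and the cumulative incidence of death too low.

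This matters here because the article wants results that generalise to lymphoma patients in the general population (Representativeness analysis), plans net survival (Clinical outcomes), and takes its planning event rate from French 1-year DLBCL survival (Sample size calculation). A population estimate that starts at diagnosis includes the early deaths that this cohort cannot contain.

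The correction that the article does foresee acts elsewhere. Weighting or adjusting on baseline covariates changes the mix of included patients. Within each covariate stratum, every included patient still carries the same death-free interval before consent.

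**Working it through.** **Inputs from the article.** Entry window: at most 180 days. Planning values: HR 1.5, exposure prevalence 10%, two-sided alpha 0.05, power 80%, 530 events, event proportion about 30%, 1-year survival 70% in the unexposed and 59% in the exposed.

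**Inputs assumed.** The diagnosis-to-consent lag is uniform over 0 to 30, 60, 90 or 180 days and independent of survival. The hazard is constant or early-peaking (Weibull shape 0.7).

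**The plan's own figures reproduce.**
- Events: (1.960 + 0.842)² / [0.10 × 0.90 × (ln 1.5)²] = 530.5 (stated 530).
- Patients: 530 / 0.3 = 1767 (stated 1767).
- Survival in the exposed: 0.70^1.5 = 0.586 (stated 59%).

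The sample size arithmetic is not in question. The 70% serves below as the true value.

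**Size of the overstatement.** A patient with survival time T and lag E is included only if T > E. For lags under one year, Kaplan-Meier from diagnosis without an entry time estimates

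P(T > 1 | T > E) = S(1) / E[S(lag)].

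The rate is λ = −ln 0.70 = 0.3567 per year. With a constant hazard and a lag uniform on 0 to a years, E[S(lag)] = (1 − e^(−λa)) / (λa). For 0-180 days, a = 180/365.25 and λa = 0.1758, so E[S(lag)] = 0.9170 and the estimate is 0.70 / 0.9170 = 0.763. For the Weibull case S(u) = exp(−λu^0.7), averaged numerically over the lag.

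| Lag, uniform | Constant hazard: E[S(lag)] | Naive 1-year survival | Weibull 0.7: E[S(lag)] | Naive 1-year survival |
|---|---|---|---|---|
| 0-30 days | 0.9855 | 0.710 | 0.9643 | 0.726 |
| 0-60 days | 0.9713 | 0.721 | 0.9428 | 0.742 |
| 0-90 days | 0.9573 | 0.731 | 0.9249 | 0.757 |
| 0-180 days | 0.9170 | 0.763 | 0.8815 | 0.794 |

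A simulation of 2,000,000 potential patients per scenario agrees to within about 0.001. Entering each patient at the consent date gave 0.699 to 0.702 in every scenario.

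**Hazard ratios, lag unrelated to exposure.** With 10% exposed and a true HR of 1.5, the naive Cox HR was 1.49 to 1.51 and the delayed-entry HR 1.49 to 1.50. The missing early deaths dilute both hazards by nearly the same factor.

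**Hazard ratios, lag related to exposure.** Same set-up, HR over the first year:

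| Lag in exposed / unexposed | True HR | Naive, constant hazard | Naive, Weibull 0.7 |
|---|---|---|---|
| 0-90 / 0-30 days | 1.5 | about 1.35 | about 1.26 |
| 0-30 / 0-90 days | 1.5 | about 1.66 | about 1.78 |
| 0-90 / 0-30 days | 1.0 | about 0.91 | about 0.85 |
| 0-30 / 0-90 days | 1.0 | about 1.11 | about 1.18 |

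Delayed entry returned 1.48 to 1.51 and 0.99 to 1.01. These unequal lags are hypothetical. The article documents no such difference.

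**The case against.** The strongest reply is that the article never says survival will be counted from biopsy. The Follow-up sentence sets due dates for data collection, and the Discussion sentence explains why visits follow clinical management. If endpoints start at inclusion, or if risk sets already use the consent date, there is no immortal time. Kaplan-Meier, log-rank, Cox and flexible parametric models all accept an entry time, so nothing written rules it out. Time origins are also often fixed in a full protocol or SAP, and neither is shown. This stands, and it makes the point conditional. It does not remove it: the article fixes the entry window, names the estimators and discusses selection, yet the remedy it names cannot restore deaths before consent.

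Stronger readings that a reader might infer are not supported:

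- **All hazard ratios are biased.** They are close to unbiased when the lag is unrelated to exposure and prognosis. The general objective and the sample size rest on hazard ratios.
- **Time to first treatment is inflated.** That is not a listed outcome. The listed one is time to next treatment, with no stated start.
- **The lag is typically six months.** The 180 days is a ceiling. Treated patients must enter before treatment other than pre-phase, so their lag cannot exceed their diagnosis-to-treatment interval.
- **The planned registry comparison is invalid.** The comparisons specified concern age and subtype distributions, not survival.

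**Conclusion.** The point holds conditionally. If OS, PFS, EFS or net survival is counted from diagnosis with the named methods and no entry time, absolute survival is overstated. On a true 1-year DLBCL survival of 70%, the excess is about 1 to 6 points under a constant hazard and 3 to 9 under an early-peaking one. For comparison, the contrast implied by HR 1.5 in the sample size section is 11 points (70% against 59%).

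The size rests on the assumed lags and hazard shapes. Where treatment starts soon after biopsy, the short-lag rows are the relevant ones. Hazard ratios move only if the lag differs by exposure or prognosis. This is a change worth making because the better method costs almost nothing and serves the population-level aims. It is not an error that undermines the cohort or its sample size.

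**What to change.** - State the time origin of each time-to-event endpoint.
- Where it is diagnosis, keep that origin and enter each patient in the risk set at the consent date: left-truncated Kaplan-Meier, log-rank, and Cox or flexible parametric models, with Aalen-Johansen with delayed entry for cumulative incidence. Apply the same entry time to net survival.
- Where it is inclusion, say so, and do not set the result beside survival counted from diagnosis.
- Report the diagnosis-to-consent lag by subtype and centre, so that readers can judge the size of the problem and whether the lag varies with patient characteristics.

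The cost is a few sentences and two dates, consent and biopsy; both events are already part of the study procedures. Intervals widen slightly in the first months, when few patients have entered. Delayed entry also assumes that the lag is unrelated to survival given the covariates. It does not bring back patients excluded because treatment began before consent, so that limit should be stated alongside the results.
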